### Elimination criteria

3.4

Those who do not meet the inclusion criteria and mistakenly accept them;Those who meet the inclusion criteria but fail to implement the trial plan after inclusion.

The reasons should be explained for excluded cases, and the case report form (CRF) form should be retained for future reference.

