### Exclusion criteria

3.3

Those with severe primary diseases such as severe cardiovascular and cerebrovascular diseases, as well as mental illness;Poor compliance and incomplete data during clinical research;The diagnosis is unclear;Subjects who cannot perform the provisions of this experimental protocol;Subjects whose observation items are incomplete and cannot evaluate the test effect and side effects;Those who have participated in other clinical trials in the past 3 months;Patients who are pregnant or breastfeeding;Those who have received other immune-related therapies or other therapies that may affect immune function;During the medication process, those who suffer from other diseases due to non-drug factors and cannot continue to complete treatment.

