### Drop-out criteria

3.5

Abnormal function of important organs of the subject during the clinical trial;The subject experienced severe drug allergic reactions during the clinical trial;Serious adverse reactions require discontinuation of trial drug treatment;Patients cannot tolerate adverse drug reactions;Poor patient compliance during the clinical study affects the effectiveness and safety evaluation, and subjects cannot be completed.

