### Randomization, allocation, and blinding

3.7

Randomized method: This study adopted a completely randomized, double-blind, placebo-controlled design. A total of 56 eligible participants were enrolled and randomly assigned at a 1:1 ratio to the experimental group and control group (28 cases per group) without stratification. The complete random allocation sequence was independently generated using SPSS 26.0 statistical software. All study drugs were uniformly coded according to the finalized random sequence, with unique drug numbers clearly marked on the outer packaging. The random sequence and allocation list were securely managed by an independent dedicated researcher who was not involved in participant recruitment, clinical assessment, sample testing, or data analysis, ensuring strict allocation concealment throughout the trial.

Blinding method: A four-level rigorous blinding strategy was implemented throughout the entire trial, with participants, clinical investigators, imaging/outcome assessors, and statistical analysts remaining fully blinded. Formal unblinding was only performed after data entry, data verification and database lock. To quantitatively assess blinding quality, a pre-specified post-trial blinding validity evaluation was conducted. Before official unblinding, all participants and attending investigators completed a standardized blinding guess questionnaire, and guessing accuracy was calculated to verify blinding efficacy and control detection bias. Emergency unblinding was only permitted for life-threatening adverse events requiring urgent clinical management, and was performed only by the principal investigator. All unblinding events were fully documented. Participants with emergency unblinding were unblinded for clinical management but remained in safety follow-up and safety data analysis. All participants provided written informed consent before enrolment.

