### Primary outcome

4.1

6-month PFS rate: the proportion of all randomized participants who are free of disease progression (assessed per iRECIST criteria) and free from all-cause death at the 6-month time-point from randomization.

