### Statistical analysis plan

4.10

Data processing was carried out with SPSS26.0 statistical software. The measurement data gives the mean, standard deviation, minimum, maximum, median, etc., which are expressed as mean ± standard deviation; the counting data gives the frequency distribution and corresponding percentages. T-test was used to compare data groups with normal distribution measurement data; rank-sum test was used for non-normal distribution measurement data, chi-square test was used for counting data, qualitative variables and correlation. Log-rank test was used for survival time and survival rate after treatment. Survival analysis was carried out using Kaplan-Meier method. Using α=0.05 as the test criterion, P<0.05 as the difference is statistically significant.

Information on the start and end times and treatment courses of antibiotics, proton pump inhibitors (PPIs), and probiotics during the trial will be collected, and key dietary covariates will be collected; subjects will not be forced to withdraw from the study due to the use of the above drugs. The preset sensitivity analysis included: excluding subjects who used antibiotics during follow-up; incorporating PPI, probiotics and dietary covariates into the model for correction to evaluate the robustness of the primary endpoint and microbiome and metabolome analysis results.

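### The elimination rule in 3.4 and the post-enrolment items in 3.3 conflict with the all-randomised primary endpoint in 4.1, and nothing confines them to a secondary analysis

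*Protocol article*

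**What the plan says.** The primary endpoint in section 4.1 of the protocol article is "the proportion of all randomized participants who are free of disease progression (assessed per iRECIST criteria) and free from all-cause death", taken at six months from randomisation. The denominator is therefore everyone randomised: 56 patients, 28 per arm.

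Other sections remove patients after that point:

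- **3.4 Elimination criteria** has two items. One concerns ineligible patients enrolled in error: "Those who do not meet the inclusion criteria and mistakenly accept them". The other concerns eligible patients: "Those who meet the inclusion criteria but fail to implement the trial plan after inclusion". The section then refers to these patients as excluded, and asks for the reasons and for their case report forms to be kept.
- **3.3 Exclusion criteria** includes "Poor compliance and incomplete data during clinical research", incomplete observations that prevent evaluation, and other illness arising while on study medication. None of these can be known at screening.
- **3.5 and 3.6** make toxicity, intolerance, poor compliance and withdrawal grounds for drop-out or discontinuation. They do not say whether follow-up for the endpoint continues.
- **3.7** says that emergency-unblinded patients "remained in safety follow-up and safety data analysis". It does not mention efficacy.
- **2.2** adds 20% for loss, taking 23 per arm to 28.

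Section 4.10 does not say how these rules relate to 4.1.

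**The concern.** Rules that remove patients and a denominator of all randomised patients cannot both be applied to the same analysis. An analyst who follows 4.1 keeps a patient who stopped taking the granules in week 4. An analyst who follows 3.4 drops that patient.

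The choice matters because compliance, completeness of data and intercurrent illness can follow from treatment or prognosis. In advanced lung cancer, a patient who stops complying or misses assessments is often one who is deteriorating. Dropping such patients removes failures preferentially. If that happens more in one arm, the comparison is no longer the randomised one. The arms receive full-dose and one-tenth-dose granules (3.8), so tolerability and adherence could differ. With 28 patients per arm, a handful of removals can change the conclusion.

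**Working it through.** **1. The plan's own figure.** Inputs from 2.2: 50% against 10%, quantiles 1.96 and 1.282.

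n = (0.5 × 0.5 + 0.1 × 0.9) / 0.4² × (1.96 + 1.282)² = 0.34 / 0.16 × 10.511 = 22.33, so 23 per arm.

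23 × 1.2 = 27.6, so 28 per arm and 56 in total. The stated sample size reproduces. The allowance of 5 patients per arm (28 − 23) shows roughly how many patients the design expects to lose.

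**2. Removal that differs by arm.** Assumptions, not taken from the documents: no true effect, 30% progression-free at month 6 in both arms, uncorrected chi-square test at two-sided 0.05. Each JPGC failure is removed with probability 0.30 and no control failure is removed.

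- Share of the JPGC arm removed: 0.70 × 0.30 = 21%, close to the planned loss.
- Apparent JPGC rate: 0.30 / (0.30 + 0.70 × 0.70) = 0.30 / 0.79 = 38.0%.
- Spurious difference: 38.0% − 30% = +8.0 points.
- Type I error by exact enumeration: 9.6%, against 5.2% with no removal.

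**3. A fixed number of JPGC failures removed, none from control.** Chance of a false finding in favour of JPGC:

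| Common true rate | None removed | 3 removed | 5 removed |
|---|---|---|---|
| 10% | 2.6% | 3.0% | 5.7% |
| 30% | 2.6% | 5.4% | 9.4% |
| 50% | 2.3% | 7.3% | 14.0% |

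**4. Equal removal.** With 20% of failures removed in each arm and a true rate of 30%, both apparent rates rise to 0.30 / (0.30 + 0.70 × 0.80) = 34.9%. The expected difference stays at zero and the type I error is about 5.2%. The inflation comes from unequal removal, not from removal as such.

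**5. One table.** 14/28 against 8/28: difference 0.214, standard error √(0.393 × 0.607 × 2/28) = 0.131, z = 1.64, p = 0.10. Without five JPGC failures, 14/23 against 8/28: difference 0.323, standard error √(0.431 × 0.569 × (1/23 + 1/28)) = 0.139, z = 2.32, p = 0.020.

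**6. Power if everyone is kept.** Assume that 20% of each arm has unknown status and is counted as failed: 50% × 0.8 = 40% and 10% × 0.8 = 8%. With 28 per arm:

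- Pooled-variance test: power 81.9%.
- The plan's own unpooled formula: 0.32 × √(28 / (0.24 + 0.0736)) − 1.96 = 1.06, so about 86%.
- For comparison, the pooled test gives 92.7% with 28 per arm and no loss, and 86.7% with 23 per arm remaining.

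**The case against.** The strongest reply is that 4.1 is the only sentence that fixes the population of the primary endpoint, and it does so correctly. Section 3.4 asks only for reasons and retained forms, and may be meant to define a per-protocol set in an analysis plan that is not shown. This is a fair reading, but the article does not state it. It calls these patients excluded without qualification and puts similar items among the eligibility criteria. The texts still have to be reconciled.

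The second reply is that participants, investigators, assessors and statisticians are blinded, which limits selective removal. That stands. The unequal removal rates above are assumptions that nothing in the documents supports. They show what is possible, not what is expected.

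A reader might also infer more than the documents support in three places:

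- **Unblinding.** It is tempting to conclude that 3.7 removes emergency-unblinded patients from the efficacy analysis. It does not say so. It confirms their place in the safety analysis and leaves efficacy open.
- **Drop-out.** It is tempting to conclude that 3.5 and 3.6 end follow-up. One item, "Serious adverse reactions require discontinuation of trial drug treatment", concerns stopping the study drug. Table 2 schedules imaging and survival after drug withdrawal, and 4.9 plans a last telephone contact for all enrolled patients. The wording is ambiguous; it does not plainly end follow-up.
- **Antibiotics and related exposures.** The analysis "excluding subjects who used antibiotics during follow-up" and the adjustment for PPIs, probiotics and diet are labelled sensitivity analyses in 4.10. They remove nobody from the primary analysis and are not part of this conflict. At most, they condition on exposure after randomisation, so agreement with the primary result would be weak evidence of robustness.

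**Conclusion.** The conflict between 4.1 on one side and 3.3 and 3.4 on the other is explicit and should be resolved before unblinding, because it decides which patients enter the primary result. This part does not rest on any assumed rate.

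Bias is possible but not established. Under the assumed 30% rate with no true effect, losing 30% of failures from the JPGC arm alone gives about +8 points and 9.6% type I error, while balanced losses give no inflation. The size depends on the underlying rate, on how many patients are removed, and above all on whether removals differ by arm. The points on drop-out and emergency unblinding are clarifications to make at the same time, not further contradictions.

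**What to change.** 1. State that the primary analysis includes all 56 randomised patients, in the arm assigned.
2. Move the items that can be known only after enrolment out of 3.3.
3. Use 3.4 only to define a supportive per-protocol set.
4. State that drop-out under 3.5 or 3.6 does not end the imaging and survival follow-up already in Table 2, except when consent is withdrawn.
5. State that emergency-unblinded patients stay in the efficacy analysis.
6. Give one rule for unknown month-6 status. An example is to count it as not progression-free, with a Kaplan-Meier month-6 estimate as sensitivity analysis. This is a convention among several; what matters is that it is fixed before unblinding.
7. Note that the antibiotic, PPI, probiotic and diet analyses condition on post-randomisation exposure and should not be read as confirming the primary result.

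The cost is mainly wording. Recruitment was still under way at submission, so the change can precede unblinding, and the follow-up is already scheduled. Item 6 carries a real statistical cost: if 20% are lost and counted as failures, the difference shrinks from 40 to 32 points, and power is about 82% by the pooled test (about 86% by the plan's own formula) against the stated 90%. The sponsor should accept that figure knowingly or limit the loss through complete follow-up.

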### Drop-out criteria

3.5

Abnormal function of important organs of the subject during the clinical trial;The subject experienced severe drug allergic reactions during the clinical trial;Serious adverse reactions require discontinuation of trial drug treatment;Patients cannot tolerate adverse drug reactions;Poor patient compliance during the clinical study affects the effectiveness and safety evaluation, and subjects cannot be completed.

### Discontinuation criteria and voluntary withdrawal of participants

3.6

If a serious adverse event occurs, the doctor judges whether the clinical trial of the case should be stopped.If serious deviations occur due to poor compliance during the implementation of clinical trial protocols, it is difficult to evaluate the drug effect.Subjects who are unwilling or impossible to continue the clinical study for whatever reason and are discontinued by submitting a request to the competent doctor to withdraw from the study.

### Randomization, allocation, and blinding

3.7

Randomized method: This study adopted a completely randomized, double-blind, placebo-controlled design. A total of 56 eligible participants were enrolled and randomly assigned at a 1:1 ratio to the experimental group and control group (28 cases per group) without stratification. The complete random allocation sequence was independently generated using SPSS 26.0 statistical software. All study drugs were uniformly coded according to the finalized random sequence, with unique drug numbers clearly marked on the outer packaging. The random sequence and allocation list were securely managed by an independent dedicated researcher who was not involved in participant recruitment, clinical assessment, sample testing, or data analysis, ensuring strict allocation concealment throughout the trial.

Blinding method: A four-level rigorous blinding strategy was implemented throughout the entire trial, with participants, clinical investigators, imaging/outcome assessors, and statistical analysts remaining fully blinded. Formal unblinding was only performed after data entry, data verification and database lock. To quantitatively assess blinding quality, a pre-specified post-trial blinding validity evaluation was conducted. Before official unblinding, all participants and attending investigators completed a standardized blinding guess questionnaire, and guessing accuracy was calculated to verify blinding efficacy and control detection bias. Emergency unblinding was only permitted for life-threatening adverse events requiring urgent clinical management, and was performed only by the principal investigator. All unblinding events were fully documented. Participants with emergency unblinding were unblinded for clinical management but remained in safety follow-up and safety data analysis. All participants provided written informed consent before enrolment.

### Intervention method

3.8

Treatment group: Jianpi Guchang granules, 1 bag each time, twice a day. Combined with immunotherapy (a. Define and stratify according to PD-L1 tumor proportion score and EGFR/ALK/KRAS/BRAF status, driver gene negative, any PD-L1 level: platinum-containing chemotherapy combined with immunotherapy is an important first-line option. When PD-L1 TPS>1% subjects, combined PD-1/PD-L1 immunotherapy is allowed. b. Choose a chemotherapy regimen that complies with guideline recommendations). There is a course of treatment every 21 days, and there are a total of 4 courses of treatment.Control group: The control group received oral granules at 1/10 of the original dose of the treatment group, and other treatment options were the same as those in the treatment group. Every 21 days is a course of treatment, and a total of 4 courses of treatment are provided.

Granules:The granules and placebo used in the trial were produced by Shanghai Wanshicheng Pharmaceutical Co., Ltd.

**Table 2** presents the timeline for subject screening, trial interventions and study assessments.

**Table 2 T2:** Trial timeline.

Visit	Screening	Drug intervention period (weeks)				After drug withdrawal	Further follow-up (Every three months until 3 months before the end of the project or the patient's death)
	0d	3	6	9	12	3 months	
Informed consent form	×						
Demographic information	×						
Inclusion and exclusion criteria	×						
General information	×						
Vital signs	×						
History of NSCLC and its treatment	×						
History of other diseases and their treatments	×						
TCM syndrome score	×	×	×	×	×		
ECOG score	×	×	×	×	×		
EORTC QLQ-C30	×	×	×	×	×		
Routine blood tests	×		×		×		
Liver function	×		×		×		
Renal function	×		×		×		
Serum and stool samples collection	×		×		×		
Intestinal barrier function	×		×		×		
Gut flora	×		×		×		
Inflammatory cytokines	×		×		×		
T cell subsets	×		×		×		
Imaging evaluation (RESIST1.1)	×		×		×	×	×
Adverse events		×	×	×	×	×	×
Release drugs/placebo	×	×	×	×			
Retrieve empty packages		×	×	×	×		
Drug combination	×	×	×	×	×	×	×
Survival					×	×	×

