Traditional Chinese medicine can increase efficiency, attenuate toxicity, delay drug resistance and improve quality of life (11, 12), It can enhance efficacy by regulating immunity and reshaping TME (13), reduce the incidence of irAEs (14), and use multi-target intervention to delay drug resistance (15). Traditional Chinese medicine regards the “spleen” as the foundation of the day after tomorrow. Patients with advanced lung cancer generally have the pathogenesis of “spleen qi deficiency”, which is manifested by fatigue, poor appetite, and loose stools. “Spleen deficiency” is closely related to low immune function, chronic inflammation and intestinal flora disorders (16–18), which are the key factors affecting the efficacy of ICIs. Jianpi Guchang prescription (The drug composition is detailed in **Table 1**) is a self-made clinical experience prescription based on the theory that “the lung and the large intestine are mutually exterior-interior”. Preliminary research by our research team found that JPGC intervention in chemotherapy patients can effectively resist the increase in intestinal mucosal permeability and intestinal inflammation caused by chemotherapy. Reaction, thereby protecting the intestinal barrier function, enhancing the body’s immunity, and promoting the recovery of intestinal flora diversity after chemotherapy (19, 20). Jianpi Guchang prescription maintains the steady state of intestinal flora and protects the intestinal barrier function by regulating the metabolism of short-chain fatty acids; at the same time, it promotes Foxp3 expression by down-regulating the activity of the PI3K/Akt signaling pathway, and indirectly regulates the tumor immune microenvironment, and ultimately exerts a tumor inhibitory effect (21). In the clinical application of patients with advanced metastatic colorectal cancer, this compound treatment has been shown to extend the median survival time of patients by 5.06 months and significantly improve the quality of life of patients. Therefore, the strategy of combining the principles of strengthening the spleen with ICIs has a solid theoretical basis and transformation potential. We designed this study to focus on the effectiveness and safety of JPGC combined with ICIs in the treatment of non-small cell lung cancer.

**Table 1 T1:** Components of JPGC prescription.

Chinese name	Latin name	Source plant	Dosage (g)

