### Inclusion criteria

3.2

A patient with pathologically confirmed non-small cell lung cancer and stage IIIB-IV who did not meet the surgical indications according to UICC version 8;It conforms to traditional Chinese medicine syndrome differentiation and is classified as spleen deficiency syndrome;Willing to receive immunotherapy;No antibiotics, systemic corticosteroids (or prednisone doses less than 10mg/day) or other immunosuppressants were used within 1 month before enrollment;No inflammatory bowel disease, radiation enteritis, rheumatic immunity and other diseases;No other serious complications;Aged between 18 and 80 years inclusive, male or female subjects;ECOG ≤ 2, estimated survival time ≥3 months;Baseline laboratory tests met the following criteria: neutrophils ≥1.5×10^9/L, platelets ≥80×10^9/L, hemoglobin ≥ 90 g/L, Serum alanine aminotransferase (ALT) and aspartate aminotransferase (AST) ≤2.5 times the upper limit of normal (if AST is allowed when liver metastasis is present, ALT ≤ 5 times the upper limit of normal), bilirubin ≤1.5 times the upper limit of normal, and creatinine ≤1.5 times the upper limit of norma, serum creatinine ≤ULN to 1.5 times, INR ≤ 1.5 or prothrombin time (PT) extension no more than 3 seconds in normal control.

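### Chemotherapy, which the article itself says affects the gut, varies between patients but is missing from the stated gut-endpoint adjustments; this costs some precision on exploratory endpoints and is nearly free to fix.

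*Protocol article*

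**What the plan says.** **Chemotherapy and the gut.** The Introduction reports the team's preliminary finding that JPGC can "effectively resist the increase in intestinal mucosal permeability and intestinal inflammation caused by chemotherapy". It adds that JPGC acts by "promoting the recovery of intestinal flora diversity after chemotherapy". Barrier damage and intestinal inflammation are therefore stated outright as chemotherapy effects. Loss of flora diversity is only implied by the word recovery.

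**Backbone.** Section 3.8 says that "platinum-containing chemotherapy combined with immunotherapy is an important first-line option". It then says "When PD-L1 TPS>1% subjects, combined PD-1/PD-L1 immunotherapy is allowed", and on the regimen: "Choose a chemotherapy regimen that complies with guideline recommendations". The only backbone requirement in section 3.2 (Inclusion criteria) is "Willing to receive immunotherapy".

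**Allocation.** Section 3.7 randomises 56 patients 1:1, 28 per arm, with no stratification. Section 3.8 does speak of stratifying by PD-L1 and driver-gene status, but in the setting of treatment choice. If it were meant for randomisation it would contradict 3.7.

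**Analysis.** Section 4.10 gives t or rank-sum tests for measurement data. Its preset sensitivity analyses exclude antibiotic users and call for "incorporating PPI, probiotics and dietary covariates into the model for correction", aimed at the primary endpoint, the microbiome and the metabolome. No adjustment is stated for barrier markers, cytokines or T-cell subsets. The workflow in 4.4 names no covariate. Section 4.3 makes all the gut and immune markers exploratory.

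**The concern.** The article chooses which gut-related exposures to adjust for and lists three. The exposure that its own rationale names as raising permeability and inflammation is not among them, although it differs between patients and is not balanced by design. These markers carry the mechanistic hypothesis in 4.4. With 28 per arm, a covariate that explains part of their variance is worth having, and one fixed before randomisation can be added without harming the comparison. What is at stake is precision on exploratory endpoints. The 6-month PFS rate and PFS are not the subject of this point.

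**Working it through.** **The plan's own figure.** The plan gives no power figure for the gut endpoints. Its sample size rests on the binary primary endpoint and reproduces: (0.25 + 0.09)/0.16 × (1.96 + 1.282)² = 2.125 × 10.51 = 22.3, rounded up to 23; 23 × 1.2 = 27.6, rounded up to 28. Only the 28 per arm is used below.

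**Assumptions (not in the documents).**
- Share on chemotherapy: q = 70%, with 50% to 80% as the wider range.
- Chemotherapy effect on a marker: e = 0.5 to 1 SD, in units of the SD within a backbone group.
- JPGC effect: 0.8 SD, the same on every backbone.

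**Step 1: variance left in the error term.** The unadjusted variance is v = 1 + q(1 − q)e².
- q = 0.7, e = 0.5: v = 1 + 0.21 × 0.25 = 1.0525, so backbone explains 1 − 1/1.0525 = 5%.
- q = 0.7, e = 1: v = 1 + 0.21 × 1 = 1.21, so backbone explains 17%.
- Over q = 50% to 80%, v runs from 1.04 to 1.25.

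**Step 2: power at 28 per arm (two-sided 5% t-test).** The standardised effect without adjustment is 0.8/√v.

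| e | Unadjusted effect | Power, unadjusted | Power, adjusted |
|---|---|---|---|
| 0.5 SD | 0.8/√1.0525 = 0.78 | about 82% | about 83% |
| 1 SD | 0.8/√1.21 = 0.73 | about 76% | about 82% to 83% |

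The adjusted figures come from simulating a linear model with arm and backbone. With perfect balance the value would be 83.6%; chance imbalance costs up to about one point. The gain is roughly 1 to 6 points.

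**Step 3: chance imbalance.** With 39 of 56 patients on chemotherapy and arms fixed at 28, the SD of the between-arm difference in chemotherapy share is 12.4 points. A difference of 20 points or more occurs in about 8% of allocations (18% if half receive chemotherapy). Such a difference would move an unadjusted estimate by 0.20 × e = 0.10 to 0.20 SD.

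**Step 4: is that an extra error?** No. For q = 0.7 and e = 1, with chemotherapy status treated as sampled independently, the variance of the unadjusted difference is (2/28) × 1.21 = 0.0864. The within-backbone part is 2/28 = 0.0714. The remainder, 0.0150, equals the variance due to imbalance, 2 × 0.21/28 = 0.0150. The unadjusted standard error already contains it, and the simulated type I error of the unadjusted test is about 5%.

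**The case against.** **The full covariate set may lie elsewhere.** This is a condensed article, 4.10 does not call its list complete, and the pre-defined scripts in 4.4 are not shown. That is fair, and it cannot be said that chemotherapy is in no model at all. But the article states its tests and names its gut covariates, so adding the missing one improves a stated method.

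**A chemotherapy-free backbone is uncertain.** The TPS>1% sentence speaks of combined immunotherapy and is followed by the instruction to choose a chemotherapy regimen. It does not clearly allow chemotherapy to be omitted. This stands: if every patient receives chemotherapy, a yes/no covariate is constant and useless. The regimen would still vary, so the covariate would have to be regimen class.

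**The endpoints are exploratory.** This also stands, and it limits the weight of the point.

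Three stronger readings are tempting, and the documents do not support them.

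- *A reader might infer bias or a false-positive risk.* Under blinded randomisation there is neither; step 4 shows that imbalance is already inside the standard error.
- *A reader might infer that JPGC acts only against chemotherapy damage, so that pooling dilutes its effect.* With 30% free of chemotherapy, 0.8 SD would become 0.7 × 0.8 = 0.56 SD, and power would fall from about 84% to 54%. But the Introduction also gives JPGC a barrier effect through short-chain fatty acids without any chemotherapy condition, and 5.3 describes correction of the imbalance that goes with spleen deficiency, which every patient must have. Nor would a covariate cure dilution: when chemotherapy worsens the marker, it recovers only about 0 to 3 points of power in that scenario.
- *A reader might infer that the article calls chemotherapy a driver of every marker.* It says so for permeability and intestinal inflammation and implies it for flora diversity. The passage on preliminary work says nothing of chemotherapy effects on T-cell subsets or metabolites.

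**Conclusion.** The point holds as a modest, nearly free improvement. The article names a determinant of its barrier and inflammation endpoints, lets it vary, does not balance it, and leaves it out of its stated adjustments. The loss is precision only: about 1 to 6 points of power for a uniform 0.8 SD effect, given 70% on chemotherapy and a chemotherapy effect of 0.5 to 1 SD. The gain shrinks with a smaller chemotherapy effect or a share nearer 100%, and for a yes/no covariate it vanishes if everyone receives chemotherapy. The randomised comparison remains valid, and the primary and secondary endpoints are not called into question.

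**What to change.** 1. Record each patient's planned backbone before randomisation: platinum chemotherapy plus ICI, or ICI without chemotherapy. Clarify the TPS>1% sentence in 3.8 first. If all patients receive chemotherapy, record regimen class instead. For patients already enrolled, take the backbone planned at entry from treatment records, while analysts are still blinded.
2. In 4.10 and the 4.4 scripts, add planned backbone to arm in the models for intestinal barrier markers, inflammatory cytokines and flora diversity. For barrier markers and cytokines this means a linear model, on a transformed scale where needed. Other omics and T-cell endpoints are optional.
3. Show the unadjusted result beside the adjusted one. Give the JPGC contrast by backbone as a preset descriptive result, without a claim of effect modification.

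**Cost.** One field at entry, a few lines of analysis text, and one degree of freedom for a two-level covariate (more if regimen class has several levels). Table 2 already records drug combinations at screening and every later visit. No treatment, visit or sample size changes.

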**Methods/design:**

The evaluation design of the JPGC clinical trial was a randomized, double-blind, placebo-controlled study. The sample size is 56, and there are 28 participants in the test group and control group respectively. The test group received JPGC, and the control group received JPGC placebo. There is a course of treatment every 21 days for a total of 4 courses. The main outcomes include 6-month PFS rate, secondary outcomes include PFS, exploratory study endpoints include TCM syndrome integral, EORTC QLQ-C30, ECOG score, intestinal barrier, intestinal flora, inflammatory cytokines, T cell subsets, etc.

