### Study design

2.1

Guided by the core theories of traditional Chinese medicine that “strengthening the body and treating cancer” and “the lung and the large intestine are mutually exterior-interior”, through Placebo-controlled randomized double-masked clinical investigation, we evaluated the efficacy of integrated traditional Chinese and Western medicine based on “Jianpi Guchang prescription” as the basic prescription in the treatment of spleen deficiency type stage IIIB-IV non-small cell lung cancer, prolonging patients ‘progression-free survival and improving their quality of life, obtaining high-level evidence-based medical evidence, and forming a standardized diagnosis and treatment plan that can be promoted.

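### The control is called a placebo, but the only description of what controls take is granules at 1/10 of the treatment dose; the passages must be reconciled and the control's content stated

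*Protocol article*

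**What the plan says.** The protocol article names the control in several places and describes it in one.

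- Abstract, Methods/design: "The test group received JPGC, and the control group received JPGC placebo".
- Section 2.1: the study is a "Placebo-controlled randomized double-masked clinical investigation".
- Section 3.7: "This study adopted a completely randomized, double-blind, placebo-controlled design".
- Section 3.8, treatment arm: "Treatment group: Jianpi Guchang granules, 1 bag each time, twice a day".
- Section 3.8, control arm: "The control group received oral granules at 1/10 of the original dose of the treatment group", with all other treatment the same as in the treatment arm.
- Section 3.8, supply: "The granules and placebo used in the trial were produced by" a single manufacturer. The dispensing row of Table 2 reads "Release drugs/placebo".

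Section 2.2 sizes the trial on 50% versus 10%, citing earlier clinical results. It does not say what the control patients in those results received.

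**The concern.** The design label and the description of the control do not agree. If 3.8 is followed as written, the contrast is full dose versus 1/10 dose, yet it would be reported as JPGC versus placebo. These are different treatment effects.

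The difference matters in this trial for three reasons.

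- A null result could not be read as no better than placebo, because both arms might have received some of the same prescription.
- Adverse events could not be set against an inert comparator.
- Section 4.4 pre-specifies that the intervention changes gut flora and metabolites, and the Introduction credits the same prescription with effects on flora and intestinal barrier. The article gives no ground for treating one-tenth of it as inactive, so between-arm microbiome differences would also lack an inert reference.

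**Working it through.** **Step 1. The passages side by side.** The abstract, 2.1 and 3.7 give the label placebo and no content. Section 3.8 gives a content, as a fraction of the treatment-arm dose, and no label. The supply sentence and Table 2 refer to a placebo as a product separate from the drug. No sentence says that the reduced-dose granules are that placebo, that the placebo contains JPGC, or that 1/10 of the dose is taken to be inactive. Two readings remain:

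- *The control contains JPGC at 1/10 dose*, whether as plain low-dose granules or as a diluted matching product. The contrast is then full versus 1/10 dose, and the label in the abstract, 2.1 and 3.7 does not describe it.
- *The control is inert.* The control sentence in 3.8 is then wrong.

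Text has to change under either reading.

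**Step 2. Reproduce the plan's sample size.** Inputs from 2.2: p1 = 0.50, p2 = 0.10, quantiles 1.96 and 1.282, 20% loss.

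n = [p1(1−p1) + p2(1−p2)] / (p1−p2)² × (1.96 + 1.282)² = (0.25 + 0.09) / 0.16 × 10.51 = 22.33, rounded up to 23. With loss, 23 × 1.2 = 27.6, rounded up to 28 per arm and 56 in total. The stated figures reproduce.

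**Step 3. Illustrate what residual activity would do.** Two assumptions are not in the documents: that 10% is the rate under an inert control, and that the low dose keeps a share f of the 40-point effect. The control rate becomes pc = 0.10 + 0.40f. Inverting the plan's formula,

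power = Φ{ (0.50 − pc) / √([0.25 + pc(1−pc)] / n) − 1.96 }.

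| f | pc | Power, n = 23 | Power, n = 28 | n per arm for 90%, before loss |
|---|---|---|---|---|
| 0% | 0.10 | Φ(3.29 − 1.96) = 91% | Φ(3.63 − 1.96) = 95% | 23 |
| 10% | 0.14 | Φ(2.84 − 1.96) = 81% | Φ(3.13 − 1.96) = 88% | 31 |
| 30% | 0.22 | Φ(2.07 − 1.96) = 54% | Φ(2.28 − 1.96) = 63% | 57 |

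Both sizes are shown because 2.2 plans on 23 evaluable per arm, whereas 3.7 randomizes 28 per arm and 4.1 defines the primary outcome over everyone randomized.

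**The case against.** **The placebo label dominates.** The abstract, 2.1, 3.7, the supply sentence and Table 2 all say placebo, against one sentence in a loosely worded article. That sentence says only granules for controls, while the treatment arm's granules are named as Jianpi Guchang. It may be a shortened account of the placebo's composition, with the rest left to the full protocol. This stands as a limit on certainty: a reader might infer that controls definitely receive active herbs, and the document does not establish that. It does not remove the conflict. The article chose to state the control regimen, and a fuller document elsewhere would not correct the published sentence.

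**Dilution is conservative.** A reader might infer that a positive finding would be invalid or biased upward. The text does not support that. The arms are randomized and otherwise treated alike. Provided that more dose does not lessen benefit, residual activity in the control pulls the difference toward zero, so a positive superiority result would understate the contrast with an inert control. The harm lies in labelling, in reading a null result, and in attributing safety and microbiome findings.

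**The power loss is hypothetical.** This also stands. The retained shares have no source in the documents, and the 54% figure comes from the larger share at the smaller n. If the 10% rate in 2.2 came from patients on the same 1/10-dose comparator, no power is lost on this account.

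**Conclusion.** The inconsistency is real and is in the current text. As written, 3.8 describes a full-dose versus 1/10-dose comparison that the abstract, 2.1 and 3.7 call placebo-controlled, and nothing connects the two descriptions. This is an unresolved contradiction about what the control is. The document does not show that a low-dose comparator was deliberately chosen, and no view is taken here on which control is right.

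The consequence is for what the trial may conclude; its validity as a randomized comparison of its two arms is not in question. The sample size arithmetic is also sound. The power figures show sensitivity under stated assumptions and are not an estimate of the trial's power. With a modest retained effect and all 28 per arm counted, power stays close to the planned 90%.

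**What to change.** 1. Reconcile the control sentence in 3.8 with the abstract, 2.1 and 3.7, and state in one place what the control granules contain.
2. If the control does contain JPGC, describe the trial as low-dose-controlled wherever the design is named, and limit the conclusion to full versus 1/10 dose. If it is inert, correct the sentence in 3.8.
3. In 2.2, state which comparator the 10% control rate came from. If it differs from the trial's control, restate the power at the planned size.

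**Cost.** Items 1 and 2 are wording. Item 3 is one added sentence if the comparators match. If they do not, it is more than wording: either a lower power is accepted and stated at 28 per arm, or the sample size grows. Recruitment is described as ongoing in 2.3, and formal unblinding follows database lock under 3.7, so all of this can be settled before formal unblinding.
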